##### Aim 2 procedures

2.1.3.3

Following eligibility confirmation through the electronic screening survey and synchronous virtual screening, Aim 2 participants will complete online self-report assessments and virtual clinician-administered assessments. Participants randomized to immediate treatment will complete assessments at baseline, post-treatment (following completion of RISE UP modules and EW sessions), and 1-week follow-up. Participants randomized to the 6-week waitlist condition will complete assessments at baseline, post-waitlist/prior to treatment initiation, post-treatment, and 1-week follow-up (see Fig. 1).

Clinician-administered assessments will include the 30-day Timeline Followback (TLFB) [129] to assess alcohol use quantity and frequency; the Structured Clinical Interview for *DSM-5* (SCID-5) Substance Use Disorders module [130] to characterize current and past alcohol/drug use disorders; and the Clinician-Administered PTSD Scale for *DSM-5* (CAPS-5) [131] to determine at least subthreshold PTSD diagnosis and symptom severity. During the baseline virtual visit, participants will schedule all planned intervention sessions and receive a scheduling handout, email reminders for appointments, and clinician contact information for rescheduling if needed. Participants will receive $50 total for completion of baseline self-report and clinician-administered assessments regardless of condition.

**Randomization.** After completion of the baseline self-report and clinician-administered assessments, Aim 2 participants will be randomized 1:1 (unstratified) using REDCap to either immediate treatment receipt or a 6-week waitlist control condition. Randomization assignments will be accessible only to the project coordinator responsible for scheduling participants into the appropriate study timeline. All other study personnel, including assessors, interventionists, and the Principal Investigator, will interact with participants using study IDs and will not be informed of whether participants were assigned to immediate treatment or waitlist. Interventionists and supervisors will know only when a participant is cleared to begin RISE, regardless of whether that occurs immediately after baseline or after the waitlist period. Clinician assessors conducting outcome evaluations will remain masked to condition assignment.

**Immediate condition.** Participants randomized to the immediate condition will begin RISE within 2 weeks following randomization. Participants will be allowed up to 6 weeks to complete the intervention, including four UP-based sessions delivered across five weeks followed by five days of EW completed within 1 week. Participants will also complete post-treatment assessments and a 1-week follow-up assessment. Limited scheduling flexibility (e.g., brief rescheduling, temporary pauses) will be permitted and documented to accommodate participant burden, availability, or clinically indicated needs while maintaining intervention and assessment sequencing.

**Waitlist control condition.** Participants randomized to the waitlist condition will complete baseline assessments identical to those completed by the immediate treatment group and then enter a 6-week wait period. Following the wait period, participants will complete a post-waitlist assessment (i.e., prior-to-treatment assessment) identical to the immediate treatment group's post-treatment assessment. Participants in the waitlist condition will then begin RISE within approximately two weeks of the post-waitlist assessment and will follow the same intervention timeline and assessment schedule as the immediate treatment group, including post-treatment and 1-week follow-up assessments. Providing RISE following the wait period is intended to maintain access to care and support ethical study conduct.

**RISE intervention.** RISE is a brief, telehealth-delivered intervention consisting of four once-weekly adapted UP skill sessions (Modules 2–5) followed by five consecutive days of EW (see Fig. 1). UP sessions will focus on understanding emotions, cultivating mindful emotional awareness, enhancing cognitive flexibility, and countering emotion-driven behaviors in contexts relevant to SMW/TGD people's experiences, such as using alcohol to cope with anticipated stigma, trauma, or difficult emotional states, and relying on avoidance coping to manage distress. Clinicians will be clinical psychology doctoral students trained in the RISE protocol.

Immediately following the four-session skills phase, participants will begin five consecutive days of EW. Participants will receive a secure REDCap link containing the daily writing prompt and a brief follow-up survey at a time jointly selected by the participant and clinician. Five writing days were selected because standard three-session EW protocols may be insufficient for reducing posttraumatic stress symptoms [80]. Participants will be instructed to write privately for 15–20 min about an experience contributing substantially to current traumatic stress, emotional distress, or alcohol-related coping, including a Criterion A trauma identified during the baseline CAPS-5 assessment, stigma-related adversity, or another distressing adverse experience. Consistent with standard EW procedures, participants will focus on their thoughts and feelings rather than grammar, spelling, or structure [83].

Following each writing session, participants will complete a brief (20–25 min) telehealth check-in with the same clinician who delivered their UP sessions. Participants may share their writing through reading aloud, screen sharing, verbal summarization, or may elect not to share the content directly. Clinicians will use process-focused discussion to monitor emotional arousal and safety, reinforce grounding and coping skills, support engagement with difficult material, and connect writing experiences to UP skills such as emotional awareness, cognitive flexibility, and reduction of emotion-driven behaviors. Discussions may include identifying emotional patterns activated during writing, examining inflexible beliefs, and applying coping strategies to manage alcohol cravings or reduce using alcohol to feel better or to cope with distressing trauma reminders, interpersonal rejection, or negative affect.

Clinicians will also provide brief psychoeducation to normalize emotional activation during writing, reinforce the rationale for sustained engagement with difficult memories and emotions, and support understanding of habituation and inhibitory learning [[79], [80], [81], [82], [83], [84],^86^,^132^]. When relevant, clinicians may contextualize identity-linked adversity within broader sociostructural experiences affecting SMW/TGD populations [18,45,85].

This hybrid format preserves privacy during the writing task while adding structured clinician support to promote safety, engagement, and skill generalization. Consistent with inhibitory learning and emotion regulation frameworks [[79], [80], [81], [82], [83], [84],^86^], the intervention pairs repeated engagement with difficult emotional material with coping and regulatory strategies. The massed writing schedule is intended to support sustained emotional processing [80,133].

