#### Trial design

2.1.1

To address Aim 2, we will conduct a pilot randomized controlled trial using a parallel, 1:1 unstratified allocation design comparing immediate treatment receipt with a 6-week waitlist control condition (see Fig. 1). Consistent with the pilot nature of the study, treatment outcome findings will be interpreted as preliminary estimates intended to inform feasibility, acceptability, and future efficacy testing. Outcome data will be collected through virtual clinician-administered interviews and online self-report assessments. Participants randomized to immediate treatment will complete assessments at baseline, post-treatment (following completion of UP modules and EW sessions), and 1-week follow-up. Participants randomized to the waitlist condition will complete assessments at baseline, post-waitlist (i.e., second baseline/prior to treatment initiation), post-treatment, and 1-week follow-up (see Fig. 1).

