**Follow-up assessments.** Participants in the immediate treatment condition will complete follow-up assessments 1 week following intervention completion. Participants in the waitlist condition will complete an equivalent assessment following the 6-week wait period (i.e., prior-to-treatment assessment), as well as post-treatment and 1-week follow-up assessments after completing RISE. Follow-up assessments will include a 30-min online self-report survey and a virtual clinician-administered assessment (∼2 h) consisting of the 30-day TLFB, SCID-5 Substance Use Disorders module, and CAPS-5. Participants will have up to 2 weeks from the target assessment date to complete follow-up procedures and will receive reminder emails. Participants will receive $50 for completing follow-up assessment (either 1-week follow-up following intervention completion for those in the immediate treatment condition or the 1-week assessment following the wait period for those in the waitlist condition).

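### The between-arm comparison visit is set by finishing RISE in the immediate arm but by a fixed 6-week wait in the waitlist arm, and non-finishers have no stated visit date

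*Protocol article*

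**What the plan says.** Trial design (2.1.1) ties the immediate arm's second assessment to treatment: "post-treatment (following completion of UP modules and EW sessions". Aim 2 procedures (2.1.3.3) repeats this and sets the limits:

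- Start: "Participants randomized to the immediate condition will begin RISE within 2 weeks following randomization".
- Duration: "Participants will be allowed up to 6 weeks to complete the intervention, including four UP-based sessions delivered across five weeks", then the writing days within 1 week.
- Slack: "Limited scheduling flexibility (e.g., brief rescheduling, temporary pauses) will be permitted and documented", with no upper limit stated.
- Content: "four once-weekly adapted UP skill sessions (Modules 2–5) followed by five consecutive days of EW".

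For the waitlist arm the same section says "Following the wait period, participants will complete a post-waitlist assessment", and describes that visit as the same as the immediate arm's post-treatment visit. Aim 2 assessment procedures (2.1.3.4) first places the immediate arm's follow-up 1 week after the intervention ends, then says "Participants in the waitlist condition will complete an equivalent assessment following the 6-week wait period". Its payment sentence describes the waitlist visit as a 1-week assessment after the wait. It allows up to 2 weeks from the target date to complete follow-up.

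The analytic plan (2.1.5.2) makes the time × arm interaction across assessment timepoints the primary clinical analysis, under intention-to-treat, with completer-only models as sensitivity analyses. Acceptability and feasibility (2.1.3.6) indexes retention by the post-treatment and follow-up assessments. For people who stop or never start, it mentions only eligibility for exit interviews.

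**The concern.** The two arms run on different clocks. One visit is triggered by something that happens after randomization and depends on how treatment goes; the other is a calendar date. Three things follow.

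1. Time since randomization at the comparison visit varies with treatment progress in the immediate arm only. Symptoms and drinking can change over a few weeks without treatment, particularly in people enrolled on symptom and drinking screens, so elapsed time is partly mixed with treatment.
2. A visit that falls due only on completion has no due date for someone who never completes. Waitlist participants have a date whatever they do. If the trigger is followed literally, missing outcomes would be linked to treatment progress in one arm, and retention would partly measure treatment completion. The satisfaction measures collected at the same visits would be affected too.
3. If the post-waitlist visit has two possible counterparts, the between-arm contrast in the time × arm model is not fixed.

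This matters even in a pilot, because retention, assessment parameters and standardized effect estimates are what it is meant to pass on to the next trial.

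**Working it through.** The article states no elapsed time to the comparison visit, so there is no figure to reproduce. The check is calendar arithmetic on the stated limits.

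**Assumptions.** The wait is counted from randomization. In the fastest case RISE starts on the day of randomization. Each visit takes place on its target date unless the window is mentioned.

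**Post-treatment, immediate arm**

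- Fastest: sessions on days 0, 7, 14 and 21, then five writing days: 21 + 5 = day 26, or 26/7 = 3.7 weeks.
- Latest start with the fastest course: 14 + 26 = day 40, or 5.7 weeks.
- Immediate start with the full allowance: day 42, or 6.0 weeks.
- Latest start with the full allowance: 14 + 42 = day 56, or 8.0 weeks; later with pauses.

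**Comparison visit, waitlist arm:** 6 × 7 = day 42, or 6.0 weeks.

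**Difference, immediate minus waitlist:** (26 - 42)/7 = -2.3 weeks to (56 - 42)/7 = +2.0 weeks. The midpoint of the immediate range is (3.7 + 8.0)/2 = about 5.9 weeks.

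**If the pairing in 2.1.3.4 is used instead:** the 1-week follow-up falls at (26 + 7)/7 = 4.7 to (56 + 7)/7 = 9.0 weeks. The waitlist visit is at 6 weeks, or 7 if the payment wording means a week after the wait. Adding the 2-week window, the latest visit is week 9 + 2 = 11 against week 6 + 2 = 8 (or 7 + 2 = 9).

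**30-day Timeline Followback** (from Aim 2 procedures)

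- Waitlist: days 42 - 30 = 12 to 42.
- Immediate, fastest: days 26 - 30 = -4 to 26, so it reaches back before randomization and shares 26 - 12 = 14 days with the waitlist period.
- Immediate, slowest: days 56 - 30 = 26 to 56, sharing 42 - 26 = 16 days with the waitlist period.

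**Non-completers**

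- 2.1.1 and 2.1.3.3: post-treatment follows completion of the modules and writing sessions.
- 2.1.3.6: completion means at least 3 of 4 skills sessions and at least 3 writing sessions. It is not said whether the visit waits for that threshold or for the full course.
- 2.1.3.6: participants who stop or never start may be interviewed where feasible; no outcome visit is named for them.
- 2.1.5.2: intention-to-treat, which needs their outcomes.
- 2.1.4: attrition of about 20% is expected, which would be 0.20 × 30 = 6 people per arm if it fell evenly.

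**Pairing.** 2.1.3.3 matches the post-waitlist visit to post-treatment. 2.1.3.4 matches it to the follow-up 1 week later and pays for it on that basis.

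**The case against.** The design shows an intention to match. Five weeks of skills sessions plus one week of writing is 6 weeks, the same as the wait, and all sessions are booked at the baseline visit. Two of the four schedules worked above land at or near week 6. A reader who takes only the 8-week limit might infer that the immediate arm is observed for longer, so that natural improvement flatters RISE. The document does not support that: the difference can go either way and its average could be near zero. What stands is that timing depends on progress in one arm only.

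A reader might also infer that the immediate arm will consist of completers set against an unselected waitlist arm. The article does not state such a rule. Completer-only models are listed as sensitivity analyses, which implies that non-completers contribute to the primary model, and retention is defined separately from intervention completion. The figure described as showing the anticipated schedule is not visible, and a fuller protocol may hold the rule. What stands is that the visible text ties the visit to completion and gives non-completers no date.

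On the pairing, both descriptions could refer to the content of the visit rather than to an analytic match. That is fair for the two descriptive sentences, but it does not explain the payment wording, which suggests a different week.

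Finally, this is a pilot. No powered test rests on the timing, and the article itself says that effect sizes should be read cautiously. That bears on severity, but retention and assessment completion are among the pilot's main products, and they depend on the same visits.

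**Conclusion.** The concern holds as a scheduling defect that should be fixed before Aim 2 starts. The immediate-arm comparison visit can fall about 3.7 to 8 weeks after randomization, against a fixed 6 weeks: a difference of about -2.3 to +2.0 weeks with no known direction. At the extremes the 30-day drinking periods of the two arms share only about half their days. The range rests on the stated limits and the fastest schedule they permit; pauses could extend it.

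The missing date for non-starters and non-completers creates a risk that outcome, retention and satisfaction data favour finishers in the immediate arm. A reader might try to size this by applying the 20% attrition to that arm and assuming how much worse the missing participants would have been. The document does not support such a figure: the 20% is overall attrition rather than immediate-arm non-completion, the gap in outcome is not given, and a mixed model uses more than the raw means of completers. The size of any bias is therefore unknown.

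The two pairings of the post-waitlist visit are a wording conflict that must be reconciled whatever else is decided. Because the trial is an estimation-focused pilot, this is a needed improvement and not a reason to reject the design.

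**What to change.** 1. Set the between-arm comparison visit in both arms at one common time counted from randomization, with the same window. The sponsor chooses the time and makes it consistent with the start limit, the completion limit and the length of the wait.
2. Offer that visit to every randomized participant, whether or not RISE was started or finished.
3. State that the post-waitlist visit pairs with this visit only, and reconcile sections 2.1.3.3 and 2.1.3.4, including the payment sentence.
4. Record actual days since randomization at every assessment.

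The cost is protocol wording and a change to the visit calendar. There are three modest drawbacks. The interval since the last session will vary, most of all for early finishers. The 1-week follow-up will have to be sequenced around the common visit. The wait may become slightly longer if the chosen time is after week 6. Aim 2 recruitment is anticipated for August 2026, so the change can be made before anyone is randomized; an assessment that was never scheduled cannot be recovered in the analysis.

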**Initial Outcome and Descriptive Trend Analyses**. We will first summarize sample characteristics, evaluate baseline comparability between study arms, and examine patterns of missingness. Baseline variables differing across arms and associated with outcomes may be included as prespecified covariates. Primary clinical outcomes will include hazardous drinking and posttraumatic stress symptom severity, consistent with the intervention's principal clinical targets. Exploratory analyses will examine selected transdiagnostic process measures aligned with the intervention model, including emotion regulation difficulties, experiential avoidance, anxiety sensitivity, negative emotionality, coping strategies, posttraumatic maladaptive beliefs, and alcohol craving, to inform future mechanism-focused trials.

Clinical outcomes will be analyzed using mixed-effects models appropriate to outcome distributions (e.g., linear models for approximately normal outcomes; generalized models for count outcomes). Primary analyses will test the time × treatment arm interaction (immediate vs. waitlist) across assessment timepoints using an intention-to-treat framework [142]. Models will include fixed effects for time, treatment arm, and time × arm interactions, relevant covariates, and participant-level random effects. Sensitivity analyses will examine completer-only models and alternative model specifications as appropriate.

Consistent with recommendations for pilot trials, analyses will emphasize estimation rather than efficacy testing. We will report standardized effect size estimates (e.g., Hedges’ *g*) with 95% confidence intervals, descriptive outcome trajectories, and preliminary clinical trends to inform refinement, feasibility assessment, and planning of a future fully powered randomized controlled trial. No interim efficacy analyses are planned.

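### The visit carrying the RISE-versus-waitlist contrast is dated by completion of RISE in one arm and by a fixed six-week wait in the other, so elapsed time can differ by arm and an early stopper has no stated visit date

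*Protocol article*

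**What the plan says.** All references are to the protocol article.

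- **Start and length of RISE, immediate arm (2.1.3.3).** People in this arm are to "begin RISE within 2 weeks following randomization. Participants will be allowed up to 6 weeks to complete the intervention". The allowance is made up of "four UP-based sessions delivered across five weeks followed by five days of EW completed within 1 week". The intervention description in the same section speaks of "four once-weekly adapted UP skill sessions" and then five consecutive writing days.
- **Comparison visit, immediate arm (2.1.1, repeated in 2.1.3.3).** The visit is "post-treatment (following completion of UP modules and EW sessions". No day after randomisation is given.
- **Comparison visit, waitlist arm (2.1.3.3).** Participants complete baseline and "then enter a 6-week wait period. Following the wait period, participants will complete a post-waitlist assessment". Its content is described as the same as the immediate arm's post-treatment visit.
- **A second pairing (2.1.3.4, follow-up assessments).** Here the waitlist visit after the six-week wait is presented as the counterpart of the immediate arm's 1-week follow-up. The payment sentence goes further and places it one week after the wait. The section also allows up to 2 weeks from the target date to complete follow-up procedures.
- **Analysis (2.1.5.2).** "Primary analyses will test the time × treatment arm interaction (immediate vs. waitlist) across assessment timepoints using an intention-to-treat framework". Hedges' g with a 95% confidence interval will be reported.

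**The concern.** Randomisation protects a between-arm comparison made at the same time since randomisation. Here one arm's clock runs to a fixed day. The other's runs to an event, finishing RISE, that depends on when the participant starts and how fast they work through it. The six-week wait looks as if it was set to match the six weeks allowed for RISE, but the lag of up to two weeks before RISE starts was not carried across.

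Two things are at stake. First, the arms may be compared at different elapsed times, so any change that comes with time alone is not fully subtracted out. For drinking, the 30-day look-back also covers a different stretch of the trial in each arm. Second, and more basic, a visit defined by completion has no stated date for someone who does not complete. Section 2.1.3.5 lets participants stop at any time, and 2.1.4 anticipates about 20% attrition. The waitlist visit has no such dependence. An intention-to-treat contrast needs the outcome in both arms whether or not treatment was finished. Section 2.1.3.6 also measures retention by completion of these assessments, so an undefined date affects a feasibility indicator too.

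**Working it through.** **Inputs.** Start on day 0 to day 14; up to 6 weeks to complete; four weekly sessions; five consecutive writing days directly afterwards; a six-week wait; a 30-day Timeline Followback (all 2.1.3.3); 30 per arm (2.1.4). Day 0 is randomisation. I assume that the wait is also counted from there.

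**1. The plan's own figure.** 5 weeks of skills sessions + 1 week of writing = 6 weeks = 42 days. This reproduces, and it equals the wait.

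**2. Immediate-arm target date.**
- Earliest: sessions on days 0, 7, 14 and 21, then writing on days 22 to 26, so day 26 (day 25 if writing starts on the day of the fourth session).
- Latest: 14 + 42 = day 56.

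**3. Mismatch with the waitlist visit at day 42.** 26 - 42 = -16 days; 56 - 42 = +14 days. The midpoint of the range is (26 + 56)/2 = day 41.

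**4. The two descriptions of the course pull in opposite directions.**
- Once-weekly sessions without a gap, then five writing days: day 26 (start day 0) to day 40 (start day 14), always before day 42.
- The full 5 + 1 weeks: day 42 to day 56, never before day 42.

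So the range straddles day 42, but the arm as a whole need not.

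**5. The other pairing (2.1.3.4).** The 1-week follow-up falls at 26 + 7 = day 33 to 56 + 7 = day 63.
- Against day 42: -9 to +21 days.
- Against day 49, if the waitlist visit is one week after the wait: -16 to +14 days.

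Neither reading removes the mismatch. If the 2-week completion window applies to the visits in step 3, actual dates run to day 70 (56 + 14) in the immediate arm and day 56 (42 + 14) on the waitlist. Permitted pauses have no stated limit.

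**6. Timeline Followback period.**

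| Visit | Days covered |
|---|---|
| Day 26 | -4 to 26, so 4 days lie before randomisation |
| Day 42 | 12 to 42 |
| Day 56 | 26 to 56 |

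**7. Scale against sampling error.** The unadjusted standard error of a standardised difference with 30 per arm is √(2/30) = 0.26. The document gives no rate of untreated change, so I ask what rate would be needed for the timing bias to equal one standard error if change is linear. With the whole immediate arm at +14 days: 0.258 × 42/14 = 0.77 SD per six weeks. With the whole arm at -16 days: 0.258 × 42/16 = 0.68 SD per six weeks. Any smaller average mismatch needs a faster rate still. Baseline adjustment would lower the standard error, and with it these thresholds.

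**The case against.** The strongest reply is about size. This is a pilot that puts feasibility first (2.1.4), emphasises estimation (2.1.5.2) and asks for caution with effect sizes (3.1). Bias in the contrast depends on the average mismatch in the immediate arm, not on individual extremes, and the permitted range lies on both sides of day 42. That stands. A reader might multiply an assumed weekly symptom drift by the extreme gaps and report a sizeable spurious effect. The document does not support this: it gives no drift, and only an arm sitting wholly at one extreme would produce it.

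A reader might also infer that natural change is uncontrolled. It is not. The waitlist absorbs the change common to both arms, and only the residual timing gap remains. What the waitlist lacks is control of expectancy, attention and nonspecific effects, which 3.1 discloses.

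Nor does 2.1.5.2 say that the model treats the two visits as the same time point. It does not say how time is coded, and it allows alternative specifications. Modelling elapsed days could therefore help, but only for visits that took place.

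Finally, a reader might infer that no visit is planned for those who stop early. Fig. 1 is described as giving the anticipated schedule and is not shown, and retention is defined separately from intervention completion. The supportable statement is that the text ties the visit to completion and states no date for anyone else.

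None of this removes the structural point. The two anchors are stated rules, not detail left to another document.

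**Conclusion.** The point holds as a defect in how the comparison visit is defined. The immediate-arm target date ranges from about day 26 to day 56 and the waitlist date is day 42. The start lag is left out of the wait, and a participant who stops RISE has no stated date, which does not fit the intention-to-treat time-by-arm analysis. Day 26 rests on a same-day start and strictly weekly sessions; day 56 rests on the latest start and the full allowance.

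The direction and average size of any bias cannot be derived from the document, and it is probably small next to the pilot's sampling error. It still enters the Hedges' g that will be reported, and Table 1 says the outcomes are to inform power calculations for a definitive trial. It should be fixed before Aim 2 recruitment, anticipated for August 2026, because visits not collected cannot be recovered. It is not a reason to doubt the trial's purpose.

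**What to change.** 1. State which immediate-arm visit is paired with the post-waitlist visit, and reconcile 2.1.3.3 with 2.1.3.4 on this.
2. Give that pair one target date counted from randomisation, the same in both arms, and hold the visit whether RISE has been finished, is still under way or has been stopped.
3. Reconcile the start lag, the completion window (including the two descriptions of session spacing) and the wait length so that both arms can share the date. The sponsor chooses the day.
4. If wanted, keep a visit after completion as a descriptive within-RISE measure.
5. Report actual days since randomisation by arm, and add a sensitivity model that uses them.

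**Cost.** The changes are to wording and to the coordinator's calendar, but there is a real trade-off between equal elapsed time and equal treatment exposure. With the present windows, a day-42 visit would catch someone who started on day 14 and uses the full allowance 28 days into RISE. That is 14 days before the end and, if the skills sessions take five weeks, before any writing. A day-56 visit would follow every permitted course, but it would see the fastest finisher 56 - 26 = 30 days after finishing and lengthen the wait by two weeks. Tighter windows would narrow both gaps.
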